**Secondary end point**

a. Reduction in complications such as liver failure with use of rupatadine. Liver failure will be diagnosed based on the following criteria. All of the 3 following criteria should be present (16).

- Absence of any previously known liver disease
- A prolonged prothrombin time of 4-6 seconds or more
- A INR of >1.5

b. Reduction in development of shock: Shock will be defined as a pulse pressure of ≤20 mmHg or a drop in the systolic blood pressure of 30mmHg or more

c. Reduction in need of colloids: use of dextran will be considered as the patient having significant fluid leakage as per National Guidelines

d. Reduction in need of blood transfusion/s: as per National Guidelines. Use of even 1 blood transfusion will be considered as the patient having significant fluid leakage

e. Reduction in duration of the illness. The first day of the illness will be defined as the day in which the patient developed fever. The day of recovery will be defined when **all** of the following 3 criteria are fulfilled:

- Patient afebrile for 24 hours
- Platelet counts of >50,000 cells/mm^3^ or a rise of 20% from the lowest value
- Return of the haematocrit to the patients baseline

f. Reduction in sleep disturbances: a reduction in sleep disturbances will be assessed by an eight point scoring system, known as the sleep condition indicator (17). This score assessed, difficulty in falling asleep, waking up in the night, quality of sleep, any effect of poor sleep in concentration, relationships, productivity and general wellbeing. The maximum score attainable is 32 and higher scores indicate better sleep quality.

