# SYNOPSIS

| Trial Title | The efficacy of rupatadine in treating dengue: a randomised, double blinded, placebo controlled trial | |
| --- | --- | --- |
| Short title | Efficacy of rupatadine in dengue | |
| Clinical Phase | Phase 2 | |
| Trial Design | Randomised, double blinded, placebo controlled | |
| Trial Participants | Patients with dengue infection | |
| Planned Sample Size | 280 with 140 each in each study arm | |
| Treatment duration | 5 days | |
| Follow up duration | 30 days of illness | |
| Planned Trial Period | 1 year | |
|  | Objectives | Outcome Measures |
| Primary | To determine the proportions of dengue patients who develop DHF when treated with and without rupatadine | Therefore, the reduction of the proportion of individuals who develop fluid leakage (DHF) will be assessed.  Evidence of plasma leakage: evidence of plasma leakage considered as detection of free fluid in the abdomen or by the presence of a pleural effusion by USScan and/or by the presence of a rise in haematocrit of >20% of the baseline. |
| Secondary | Investigate whether rupatadine treatment leads to a. reduction in complications such as liver failure.  b. Reduction in development of shock:  c. Need of colloids:  d. Need of blood transfusion/s:  e. Duration of the illness.  f. Sleep disturbance | Liver function tests, blood clotting, colloid infusion volumes, blood transfusion volumes, length of acute illness, sleep scores. |
| Investigational Medicinal Product(s) | Rupatadine 40mg | |
| Formulation, Dose, Route of Administration | Four 10mg tablets of rupatadine to be given orally, and placebo | |

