The number of adverse events (AE) were similar in those on rupatadine 40mg and on the placebo and all AE completely resolved (Table 1). Two patients (2.98%) in the placebo group developed a SAE, namely acute liver failure. AE such as hepatitis (ALT>250U/L) was more frequent in those on the placebo as 6 (8.9%) patients developed hepatitis when compared to 3 (4.5%) on rupatadine 40mg. Severe thrombocytopenia (<5×10^9^/L) was seen in one patient in the placebo group. However, thromobocyotopenia and hepatitis are known features of dengue and therefore, unlikely to be due to drugs.

|  | Rupatadine 40mg  N=66 | Placebo  N=67 |
| --- | --- | --- |
| Abdominal pain (%) | 17 (25.7) | 21 (31.3) |
| Vomiting (%) | 21 (31.8) | 21 (31.3) |
| Diarrhoea (%) | 27 (40.9) | 24 (35.8) |
| Hepatitis (%) (ALT>250/L) | 3 (4.5) | 6 (8.9) |
| Low platelet counts  <20 ×10^9^/L (%)  20 to 50×10^9^/L (%) | 12 (18.2)  17 (25.7) | 14 (20.9)  21 (31.3) |
| High ALT (>200 U/L) (%) | 9 (13.6) | 12 (17.9) |
| High AST (>200 U/L) (%) | 14 (21.2) | 18 (26.9) |
| Low white cell count  (<1×10^9^/L) (%) | 0 (0) | 0 (0) |

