**Specific objectives**

To assess the effect of 40 mg of rupatadine in reduction of the incidence of DHF

- To determine the effect of 40 mg of rupatadine on reduction of incidence of complications associated with DHF such as acute liver failure, hepatitis, the need for colloids, significant bleeding manifestations
- To determine if rupatadine reduces the duration of post illness fatigue and sleep disturbances

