**Exclusion Criteria**

- Those who already have fluid leakage
- Fever for >3 days
- pregnant women
- those who have known allergies to antihistamines
- Individuals who are homeless, who are dependent on alcohol dependence or abuse drugs as it will be difficult to monitor these patients in the community
- Those who are unable to take the drugs orally
- Those who have known hepatic impairment defined as: All of the 3 following criteria should be present (16). Patients will be inquired about pre-existing liver disease and their clinical records accessed to find out if they have any of the following.
- Absence of any previously known liver disease
- A prolonged prothromin time of 4-6 seconds or more
- A INR of >1.5
- Those with known renal impairment will be defined as those who fulfill either of the following criteria regardless of age, hypertension and diabetes (23). Patients will be enquired regarding presence of diabetes and hypertension and will be enquired regarding any pre-existing renal disease (annexure 1). Their clinical records will be accessed to determine if they have any of the following.

- predicted GFR <60 ml/min per 1.73 m^2^

- Hereditary kidney disease

- Recurrent or extensive nephrolithiasis

Those with other pre-existing medical conditions that the PI considers may impact on interpretation of the study.

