## 9.5 Concomitant Medication

- Any patients on regular treatment for diseases such as hypertension, diabetes, asthma or any other chronic illness will be asked to take the medication as usual
- They will also take any other medicines such as paracetamol prescribed by the treating physicians as per National Guidelines
- Over the counter medications will not be permitted.

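### Liver failure is defined by two cut-offs on the same clotting test, with no evidence of liver injury required, so a non-hepatic coagulopathy that passes both is counted as liver failure

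*Protocol*

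**What the plan says.** Under Secondary end point, item a, liver failure is diagnosed when three criteria are all met, with a published review cited as the source:

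- "Absence of any previously known liver disease"
- "A prolonged prothrombin time of 4-6 seconds or more"
- an INR above 1.5

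Other parts of the protocol bear on this definition:

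- **Synopsis.** The secondary outcome measures begin "Liver function tests, blood clotting, colloid infusion volumes", so both liver tests and clotting were meant to inform the secondary objectives.
- **Specific objectives.** Liver failure and hepatitis are separate items: "complications associated with DHF such as acute liver failure, hepatitis, the need for colloids".
- **Trial Design, Data collection.** Liver function tests are mentioned for outpatients. For admitted patients they are described as routine and are recorded.
- **Background and Rationale.** The earlier trial is reported with transaminase cut-offs: "AE such as hepatitis (ALT>250U/L) was more frequent in those on the placebo". Table 1 there also uses 200 U/L for ALT and for AST. Two placebo patients (2.98%) had acute liver failure.
- **Exclusion Criteria.** The same three-item list is reused to define known hepatic impairment. Anticoagulant use and clotting disorders are not named. A general clause covers "Those with other pre-existing medical conditions that the PI considers may impact on interpretation of the study".
- **Section 9.5.** Patients on regular treatment for named conditions or "any other chronic illness will be asked to take the medication as usual".

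**The concern.** An endpoint called liver failure should need some evidence that the liver is injured. Here one criterion only removes patients with a known history, and the other two are two readings of one clotting test. A normal transaminase result would not stop a patient from being counted, and neither would an evident non-hepatic reason for a long prothrombin time.

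What is at stake is interpretation. A difference between arms in this count would be reported as a difference in liver failure, although the rule as written counts a clotting abnormality. Because few events are expected, a small number of non-hepatic cases could be a noticeable share of the total.

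The range in seconds adds a smaller problem. It is not a single cut-off and names no reference value, so two assessors could apply it differently.

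**Working it through.** The protocol gives no figure to reproduce here. The check has three parts.

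**1. What each criterion measures**

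| Criterion | What it is | Evidence of current liver injury? |
|---|---|---|
| No known liver disease | History item; only removes patients | No |
| Prothrombin time prolonged by a stated number of seconds | Clotting test | Not by itself |
| INR above 1.5 | The same test, rescaled | Not by itself |

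The definition contains no transaminase, bilirubin, encephalopathy or other liver finding, and no clause on other causes of prolongation. Liver function tests appear in the Synopsis and in Data collection, but nothing ties them to this rule.

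**2. How far the two laboratory criteria overlap**

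Formula: INR = (PT / control PT)^ISI, where ISI is the reagent's sensitivity index. Prolongation at INR 1.5 = control PT × 1.5^(1/ISI) − control PT.

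The protocol gives neither the control PT nor the ISI. I assume control PT 11 to 14 s and ISI 1.0 to 1.4.

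| Control PT (s) | ISI | Prolongation at INR 1.5 (s) | INR at +4 s | INR at +6 s |
|---|---|---|---|---|
| 11 | 1.0 | 5.5 | 1.36 | 1.55 |
| 11 | 1.4 | 3.7 | 1.54 | 1.84 |
| 12 | 1.0 | 6.0 | 1.33 | 1.50 |
| 12 | 1.3 | 4.4 | 1.45 | 1.69 |
| 12 | 1.4 | 4.0 | 1.50 | 1.76 |
| 14 | 1.0 | 7.0 | 1.29 | 1.43 |
| 14 | 1.4 | 4.7 | 1.42 | 1.65 |

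Within these assumptions, INR 1.5 corresponds to 3.7 to 7.0 s of prolongation, which straddles the stated 4 to 6 s.

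- If the line is read as 4 s or more, it is almost always redundant. The INR criterion is the stricter one except at the corner with control PT 11 s and ISI 1.4.
- If it is read as 6 s or more, it often raises the effective threshold, for example to INR 1.69 at control PT 12 s and ISI 1.3.

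On either reading it adds no independent evidence about the liver.

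**3. How rare the endpoint is**

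- Earlier trial, placebo: 2/67 = 2.98%.
- Scaled to 140 per arm (Synopsis): 2/67 × 140 = 4.2 events.
- The exact 95% interval for 2/67 is 0.4% to 10.4%, which gives 0.5 to 14.5 events per 140.

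The scaling is only indicative. The earlier trial recruited in a hospital dengue unit up to day 5 of illness, whereas this one recruits outpatients at about 3 days or less. The protocol does not say how acute liver failure was defined in the earlier trial.

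**The case against.** The strongest defence has four parts.

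**The definition is cited.** The criteria are attributed to a review of acute liver failure that is not available here, so it cannot be said whether the protocol follows its source or left something out. That is true. It does not alter how the rule works as written.

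**Not every coagulopathy counts.** A reader might infer that any clotting abnormality qualifies. It does not: it must pass both cut-offs in a patient without known liver disease. This limit stands.

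**The anticoagulant case is hypothetical.** A reader might infer that treated patients will be counted as failures from entry. Nothing in the protocol suggests that such patients will enrol in any number. Participants are aged 18 to 60, a detailed history is taken (8.5), and the general exclusion clause lets the investigator keep them out. Randomisation balances prior use on average. What stands is that no provision requires their exclusion and section 9.5 has regular medication continued. The defect does not depend on them.

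**Liver injury is captured elsewhere.** Hepatitis is a separate objective and liver function tests are recorded, so a reader could look at both. Keeping the two complications apart is a legitimate choice, and it argues against simply making ALT above 250 U/L, the earlier trial's hepatitis cut-off, a condition of liver failure. It does not justify giving the name liver failure to a count that needs no liver finding.

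**Conclusion.** The point holds as a fault in a stated rule. Followed literally, item a counts a patient without known liver disease as a liver failure when a non-hepatic coagulopathy passes both prothrombin cut-offs. The second cut-off mostly repeats the first, and its range leaves the threshold open to two readings. The overlap figures depend on the assumed control PT and ISI; the absence of any liver-injury component does not.

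The size and direction of any distortion cannot be derived from the protocol. Two stronger readings should be resisted:

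- **That a fixed fraction of events would be wrong.** One or two misclassified patients would be 1/4.2 = 24% or 2/4.2 = 48% of the indicative count, but the one or two is itself an assumption and the base is 2 of 67.
- **That less bleeding on rupatadine would be reported as liver protection.** Significant bleeding in the earlier trial was 6 (8.9%) on placebo and 2 (3%) on rupatadine, but no clotting results are given for those patients. The documents do not show that the bleeding came with a prolonged prothrombin time.

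The consequence is limited to one rare secondary endpoint that is hard to interpret as a liver effect. The primary endpoint is not affected.

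**What to change.** For counting this endpoint:

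1. Keep one coagulation criterion with one cut-off, the INR above 1.5 already stated, and drop the range in seconds.
2. Prespecify two groups among patients who meet it: with and without concurrent transaminase elevation, taken from the liver function tests already recorded. Call only the first group liver failure and report the second as coagulopathy.
3. Have the investigators set the transaminase threshold and the time window that counts as concurrent. The reporting cut-offs in Background and Rationale (ALT above 250 U/L; ALT or AST above 200 U/L) are candidates.
4. Flag anticoagulant use at baseline for these patients and show it with the result. Barring them from being counted would hide a true liver failure in a treated patient.
5. Reconcile the Exclusion Criteria with item a. The same three criteria define known hepatic impairment there, where requiring the absence of known liver disease contradicts the purpose of the exclusion. The investigators must decide what that criterion should say.

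The cost is wording and one extra line in the results table. The downside is that slightly fewer events will be counted as liver failure.

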# TRIAL DESIGN

This study is a randomized, double blinded, placebo controlled trial. The efficacy of the drug will be measured by how well it will be able to it reduce the proportion of patients who develop DHF. As secondary endpoints we hope to evaluate if it reduces the proportion of patients requiring hospital admission and also complications associated with dengue.

**Selection of patients**: Patients, who are suspected to be having a dengue infection, will be tested for dengue NS1 antigen test. These tests will be done free of charge for all patients with suspected dengue infection at the OPDs of the respective hospital. The patients who are confirmed to be having acute dengue infection and who fulfil the inclusion criteria and who do not have the exclusion criteria will be approached by a member of the team of investigators or by a medical officer of the unit who will be specially trained in obtaining informed written consent.

At the initial visit they will be assessed for the presence of dengue warning signs, their blood pressure and pulse rate recorded and a base line FBC done. They will be advised to come to the OPD for daily assessments and will be asked to come sooner if they develop persistent vomiting, feeling faint or develop any bleeding manifestations. They will be asked not to take any other over the counter drugs apart from any drugs given from the hospital (paracetamol) as per standard management of dengue.

**Data collection:** An interviewer administered questionnaire will be used to record basic demographic details of the patient. In those who are only assessed in the OPD setting (those who do not require hospital admission), basic demographic details, any co-morbid illnesses (diabetes, hypertension, asthma and allergic rhinitis), clinical features along with the daily full blood counts (FBCs) will be recorded liver function tests (Annexure 1). If the patient is admitted to hospital, additional clinical data such as hepatomegaly, presence or absence of serous effusion and additional investigations such as liver function tests, which are routinely done as standard management of dengue will be recorded (Annexure 2).

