# PARTICIPANT IDENTIFICATION

**Patient recruitment:** Patients with a suspected dengue infection, between the ages of 18 to 60, will be recruited from the OPDs of the NIID following informed written consent.

**Inclusion criteria**: All patients with confirmed dengue infection by a positive dengue NS1 antigen detection test who give informed written consent and who fulfil **all** of the following criteria will be recruited.

- **Age:** between 18-60
- **Duration of illness**: <3 days and who do not show any evidence of vascular leak. This is because in our earlier phase 2 trial, we found that the complications and the reduction in proportion of patients developing DHF was less when given early (3 ≤ days).
- **Evidence of dengue infection:** Dengue NS1 antigen test will be done in these patients and only those who are dengue antigen positive will be included. Although the sensitivity of the NS1 is less in those who are infected with the DENV-2 serotype, and even though those who are NS1 negative can also be having dengue, we will only include those who have are NS1 positive, as we believe it is important to have some evidence that the patient is infected with the dengue virus at the time of recruitment. The virus serotype and the viral loads will be done in all patients at the Centre for Dengue Research (please see below for details).

The dengue NS1 antigen will be done by rapid immununochromatographic assays (rapid strip tests) at the OPD.

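### The recovery rule behind duration of illness can date a patient recovered before a later leak, or while fluid is visible on ultrasound

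*Protocol*

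**What the plan says.** Duration of illness is item e of the protocol's secondary endpoints. It runs from the first day of fever to the day of recovery. The rule for that day is: "The day of recovery will be defined when all of the following 3 criteria are fulfilled". The criteria are:

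- Fever: none for a full day.
- Platelets, where either branch is enough: "Platelet counts of >50,000 cells/mm^3^ or a rise of 20% from the lowest value"
- Haematocrit, with no tolerance given: "Return of the haematocrit to the patients baseline"

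The Patient follow up text under Trial Design repeats the same three criteria and adds no further condition.

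Three other places bear on how the rule works:

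- **Entry state** (Participant Identification): illness of "<3 days and who do not show any evidence of vascular leak".
- **Baseline** (Trial Design): at the initial visit patients have "their blood pressure and pulse rate recorded and a base line FBC done".
- **Leakage** (Primary Study Endpoints): free abdominal fluid or a pleural effusion on ultrasound counts as leakage on its own. A haematocrit rise above 20% is an alternative, not an added requirement.

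**The concern.** The three criteria describe a patient who has come through the illness, but they are also the state of many patients who have not yet reached its critical phase. The rule does not ask that the platelet low or the haematocrit peak has passed, that the criteria hold on later days, or that leakage is absent. One patient could therefore be counted as leaking for the primary endpoint and as recovered for item e on the same day. Another could have a recovery date that precedes the leak.

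The drug is being tested because it may reduce leakage. A duration endpoint that can stop before the leak, and that cannot see ultrasound fluid, may miss the part of the illness where an effect is expected.

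**Working it through.** The protocol states no design figure to reproduce here. The check has two parts: the logic of the rule, and how often the platelet criterion carries information.

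**1. The rule, read literally**

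Recovered on a day = (afebrile for at least 24 h) AND (platelets > 50,000 OR platelets ≥ 1.2 × lowest value) AND (haematocrit at or below baseline).

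Applied to constructed patient states, which are illustrations and not trial data:

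| State | Afebrile 24 h | Platelets now / lowest so far | Haematocrit now / baseline | Result |
|---|---|---|---|---|
| No platelet fall or haematocrit rise yet | yes | 150,000 / 150,000 | 40 / 40 | recovered |
| Ultrasound fluid present, platelets at their lowest so far | yes | 60,000 / 60,000 | 40 / 40 | recovered |
| Still febrile | no | 150,000 / 150,000 | 40 / 40 | not recovered |
| Haematocrit 10% above baseline | yes | 150,000 / 150,000 | 44 / 40 | not recovered |

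The first row is a patient who may still leak later. The second is a patient who already has leakage under the primary endpoint definition. The last two rows show that fever, and any haematocrit above baseline, do hold recovery back.

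**2. What is already true at entry**

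Haematocrit equals baseline at entry because the entry blood count is the baseline. The platelet criterion is met at entry by anyone above 50,000, since no earlier fall is required. For those patients the only criterion left to satisfy is 24 afebrile hours.

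**3. How often the platelet criterion separates patients**

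The inputs are the low-platelet rows of Tables 1 and 2 in Background and Rationale, taking the two bands (below 20,000; 20,000 to 50,000) as mutually exclusive. Number in neither band = N − (lower band + upper band).

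| Group | Calculation | In neither band |
|---|---|---|
| Table 1, placebo | 67 − (14 + 21) = 32 | 32/67 = 48% |
| Table 1, rupatadine 40 mg | 66 − (12 + 17) = 37 | 37/66 = 56% |
| Table 2, early recruits, placebo | 21 − (5 + 7) = 9 | 9/21 = 43% |
| Table 2, early recruits, rupatadine | 17 − (2 + 7) = 8 | 8/17 = 47% |

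For these patients the platelet criterion is met on essentially every day.

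**4. What cannot be computed**

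A misdated recovery needs 24 afebrile hours to fall before the leak, or during it with haematocrit at baseline. The protocol gives no times of fever end against leak onset. The percentages in step 3 describe one criterion and are not a misdating rate.

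**The case against.** The strongest reply is that recovery needs all three criteria together, so a platelet criterion that is often met proves little, and the fever criterion is a real barrier. That stands, and it is why no misdating rate is claimed.

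A second reply is that return to baseline, and a rise from the lowest value, describe a course already run. This does not rescue the rule. If return required an earlier rise, a patient whose haematocrit never rose could never recover. The platelet criterion is also an either/or, and its first branch needs no fall. It is true that the text does not say first day and does not call a date final. But it gives no rule for withdrawing one either.

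A reader might infer more than the documents support:

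- **Ascites without haematocrit rise.** In Table 2, 9 of 21 early placebo recruits had ascites and 4 had a rise above 20%, so at least 5 with ascites had no such rise. It does not follow that nothing held their recovery back: the criterion is return to baseline, and a smaller rise also blocks it.
- **Effusion maximum on day 8 against a median duration of 7 days.** The first figure is from the whole earlier trial and the second from early recruits. How that trial defined duration is not given. If it used the same rule, the interquartile ranges (6 to 8.5 and 5.5 to 7) suggest that very early recovery dates were not common.
- **Visits lapse after recovery.** The sentence on visits after recovery concerns travel payment. Patient follow up asks for daily attendance, and section 8.6 sets five acute visits and a day-14 visit, with no release on recovery.
- **Paracetamol masks fever.** Section 9.5 does allow it: "They will also take any other medicines such as paracetamol prescribed by the treating physicians as per National Guidelines". It applies to both arms, no data on its effect are given, and an antipyretic-free condition would delay recovery in patients who take it only for aches.

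**Conclusion.** The point holds as a defect in the definition of one named secondary endpoint. As written in both places, the rule can date a patient recovered before a later leak, or on a day when ultrasound fluid is present and haematocrit is at baseline. This is a fixed rule that can give a wrong date, not detail left for an analysis plan.

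It rests on three assumptions: the baseline haematocrit is the entry value, return to baseline means at baseline, and the two low-platelet bands do not overlap. In the earlier trial the platelet criterion carried no information in roughly half of patients (43% to 56% across the four groups).

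The number misdated is unknown, and so is the direction of any bias. It may be tempting to say that the sicker arm would look better, but no figure in the protocol shows this, and the early-recruit platelet shares are similar by arm (43% and 47%). The primary endpoint and the visit schedule are not affected.

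**What to change.** Change the definition in item e and in Patient follow up, for outcome measurement only:

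1. Define the recovery day retrospectively, as the first day from which all three criteria hold through the remaining acute-phase assessments.
2. State a tolerance around baseline haematocrit, so that a trivial later reading does not cancel recovery.
3. Void a provisional date if leakage, as defined for the primary endpoint, is first detected afterwards. The duration then runs until the criteria are met again.
4. For patients scanned in the ward, state that a day on which fluid is newly present or increasing does not count as recovered.

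Daily blood counts, temperature and ward scans are already planned, so the work is mainly in the wording. The costs are somewhat longer durations, less comparability with the earlier trial, and some patients censored at their last acute visit. Item 4 applies only to admitted patients, because the daily scans are done in the ward, and the text should say so.
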